### Outcome parameters

#### 1. Primary outcome measures

##### Stress, anxiety and depressive symptoms

We will include the Hospital Anxiety and Depression Scale (HADS) to measure symptoms of anxiety (HADS-A: e.g., "Worrying thoughts go through my mind") and depression (HADS-D: e.g., "I feel as I am slowed down") in DM patients [37]. The self-report scale consists of 14 items, answered on a 4-point Likert scale, with the HADS-A and HADS-D both comprising 7 items (*0-3*). The score range for the anxiety and the depressive symptoms subscales is 0 to 21. The HADS has been validated in the general population and in somatic and psychiatric patients [38,39]. It has been shown to be a valid and reliable instrument with Cronbach's α ranging from 0.67 to 0.93 for the two subscales [37-39].

The Dutch version of the Perceived Stress Scale (PSS) will be included to measure general perceived stress (the degree to which situations in one's life are appraised as stressful) (e.g. "In the last month, how often have you felt nervous and stressed?"). It has been shown to be a reliable measure with Cronbach's α ranging from 0.84 to 0.86 [40]. The present version consists of 10 items which are answered on a five-point Likert scale, ranging from 'never' to 'very often' *(0-4) *[41].

The short Dutch version of the Profile of Mood States (POMS) [42] will be used to assess transient, fluctuating mood states. The scale consists of 32 adjectives about positive and negative mood states which have to be rated on a five-point Likert scale *(0 = not at all, 4 = very much) *based on how well each item describes one's mood during the last couple of weeks. For the interpretation of the results the items are divided into five subscales: Tension-anxiety (6 items); Depression-dejection (8 items); Anger-hostility (7 items); Vigor-activity (5 items); and Fatigue-inertia (6 items). The scale has sufficient consistency reliability and construct validity, with Cronbach's α's of the five subscales varying between 0.82 and 0.91 [42,43].

##### Diabetes specific emotional problems

We will include the Dutch version of the self-report questionnaire Problem Areas in Diabetes Survey (PAID), which consists of 20 statements about common negative feelings related to living with diabetes (e.g., "Feeling depressed when you think about living with diabetes", "feeling discouraged with your diabetes regimen") [44]. The items are rated on a six-point Likert scale *(1 = not a problem, 6 = a serious problem)*. PAID scores are transformed to a 0-100 scale, to facilitate interpretation [45]. A higher score indicates more emotional distress, with a cut-off score of 40 indicating seriously elevated emotional distress [46]. Factor analysis revealed that the factor structure can be represented by a one factor model (PAID total: emotional adjustment) and a four factor model (subscales: emotional problems, treatment problems, food problems, and lack of social support) [45]. We will examine the results with both models. The survey has proven to be a reliable measure, with a Cronbach's α of 0.95 for the one factor model. For the four factor model the Cronbach's α's are in range of 0.93 (emotional problems), 0.74-0.76 (treatment problems), 0.70-0.74 (food problems), and 0.69-0.72 (lack of social support) [45]. In addition, research in Dutch and American patients found support for convergent and discriminative validity of the PAID [45,47].

#### 2. Secondary outcome measures

##### Quality of life

We will include the Dutch version of the Short-Form Health Survey (SF-12) to measure health related quality of life. The self-report scale consists of 12 items that are grouped into two component summary scores: a physical (PCS) and a mental component score (MCS). Both component scores are measured on a scale from 0 to 100, with a high score indicating good health related quality of life. The SF12 has proven to be a valid and reliable measurement [48].

In addition, we will use three items of the WHOQOL-BREF [49] to measure satisfaction with oneself and life in general: "How much do you enjoy life?"; "To what extent do you feel your life to be meaningful?"; "How satisfied are you with yourself?". The questions will be analyzed separately at item level if Cronbach's α will show to be below 0.65.

##### Mindfulness

To measure mindfulness we will include the Dutch version of the Five Facet Mindfulness Questionnaire (FFMQ). FFMQ is based on a factor analytic study of five independently developed mindfulness measurement scales [50]. The factors we will use are: *Observing*, which refers to noticing or attending to internal and external experiences, such as thoughts, sensations, emotions, sounds, sights, and smells; *Acting with awareness*, which includes attending to one's activities in the present moment; *Non-judging of inner experience*, which refers to taking a non-evaluative attitude toward thoughts and feelings; and *Non-reactivity to inner experience*, which includes allowing thoughts and feelings to come and go, without getting caught up in or carried away by them [51]. The factor *Describing *will be omitted, because describing one's emotions and feelings is not a primary focus of MBSR/MBCT and we do not want to burden our patients unnecessarily. Each factor consists of 7 or 8 items, which will be answered on a five-point Likert scale (*1 = never or very rarely true, 5 = **very often or always true*). The four facets demonstrated adequate to good internal consistency (alphas ranging from 0.75 to 0.87) [50].

Changes in diabetes-specific mindfulness and acceptance processes will be assessed by the Acceptance and Action Diabetes Questionnaire (AADQ) [26]. This self-report questionnaire consists of 11-items that are answered on a 7-point Likert scale. It measures acceptance of diabetes-related feelings and thoughts and the extent to which they interfere with valued action (e.g., "I avoid thinking about what diabetes can do to me") [26]. For this measure, a Cronbach's α of 0.94 has been reported [26].

##### Self-esteem

Self-esteem will be measured by the Dutch version of the Rosenberg Self-Esteem Scale (RSES), wherein self-esteem is defined as a person's overall evaluation of his or her worthiness as a human being [52]. The questionnaire consists of 10 items answered on a four-point Likert scale, ranging from 'I totally disagree' to 'I totally agree'. A sample item is "I take a positive attitude toward myself". A higher score reflects a higher global self-esteem. The Cronbach's alpha was .86, indicating a high internal consistency [52].

#### 3. Tertiary outcome measures

##### Self-care behavior

Self-care behavior (or self-management) will be assessed with the Amsterdam Diabetes Self Care Inventory (ADSCI). The questionnaire has 11 items, which will be examined separately. Each item is divided into three or four subquestions. Higher scores indicate higher levels of self-care. The questionnaire is developed by colleagues of the VU University Medical Center in Amsterdam and used in previous trials [53,54]. The psychometric properties of the ADSCI have not yet been published.

##### Glycemic control

To measure glycemic control we will consult the three-monthly standard measurements of HbA1c of the hospital, which are documented in the hospital's patient database. The percentage HbA1c is a function of the glucose concentration to which the red blood cells are exposed and gives an indication of the average blood glucose concentration of the preceding six to eight weeks [3].

##### Blood pressure

The patients' blood pressure will be measured by an ambulant device, called the Mobil-O-Graph, which is based on the oscillometric method and which has been shown to provide reliable and valid assessments [55]. The patients, who have elevated high blood pressure (≥ 140 mmHg systolic or 90 mmHg diastolic of the mean values of 3 measurements) during the interview, will wear the meter 24 hours following the interview. The ambulatory measurements will occur two times per hour. To keep the burden for the patients as low as possible, we decided to measure the blood pressure only during the daytime. The device will be attached to the patient by the researcher who does the interviews ([name]).

#### 1. Additional outcome measures

##### Personality

To measure personality dimensions we will use the subscale Extraversion (EPQ-E) of the shortened revised Eysenck Personality Questionnaire (EPQ-RSS) and the DS-14 to measure Type D personality. Persons with a Type D personality tend to experience high levels of emotional distress, but do generally not express these emotions. For the EPQ-E, the subscale Extraversion reflects sociability, assertiveness, and the tendency to experience positive emotions. The subscale consists of 12 dichotomous (yes/no) items [56]. The Committee on Test Affairs Netherlands rates the EPQ to be a reliable measure [57].

The 14-item Type D scale (DS14) measures both negative affectivity (NA) (e.g. "I often feel unhappy"; 7 items) and social inhibition (SI) (e.g. "I am a closed kind of person"; 7 items) [58]. Items are answered on a five-point Likert scale ranging from 'false' to 'true' *(0-4)*, with the score range for the NA and SI subscales being 0 to 28 [58]. We will use the standardized cut-off ≥ 10 on both subscales to identify Type D caseness [58,59]. The DS14 has been shown to be a valid and reliable instrument, with Cronbach's α of 0.88 and 0.86 and a 3-month test-retest reliability of r = 0.72 and 0.82 for the NA and SI subscales, respectively [58]. Furthermore, a recent study showed that Type D personality is a stable construct over an 18-month period and is not confounded by disease severity and measures of anxiety and depression [60,61]. Results from a study by Denollet et al [62] suggest that particularly the interaction between NA and SI is predictive of adverse health outcomes, more than the single traits [62].

##### Demographic and clinical variables

Demographic variables will be collected by means of a questionnaire, which will be completed by the patients during the baseline assessment. Data will be collected regarding the participant's age, marital status, education, and job status. In addition, the baseline questionnaire will be used to gather information on history of emotional problems and use of psychotropic medication, level of meditation experience, sleep quantity and quality, participant's perceived importance of adequate blood glucose regulation, and amount of participant's effort to manage their blood glucose. Furthermore, the baseline questionnaire will be used to assess clinical data, such as length and weight of participants, last HbA1c, number of severe hypoglycemic episodes and/or hospitalizations because of a diabetic coma during the past year, existing diabetes complications, co-morbidities, and smoking and drinking behavior. The clinical variables (which are available) will also be retrieved from the hospitals' patient information database.

#### 1. Additional process measures

During the intervention process data will be collected, like drop-out, patients' attendance of the sessions, patients' adherence to the home work assignments, and trainers' adherence to the protocol. The adherence to the protocol will be determined each session by the trainers by means of the completion of a checklist including all components of each session. The components are divided into important and less important, facilitating decision making when time constraints are present.

### Statistical analyses

#### Sample size and power calculation

The total number of patients that have to be included and complete the study is 160, with 80 patients in each arm, taking into account a medium effect size, a power of 0.80, an alpha of 0.05, patient attrition, and subgroup analyses involving two equally sized groups (e.g. yes vs. no complications). It is expected to reach this number of participants during the course of the study.

#### Planned analyses

Repeated measures analysis of variance ((M)ANCOVA) will be used to test the hypotheses concerning the differences between groups on the dependent variables over time. In these tests age, sex, and co-morbidity will be included as covariates, in addition to those other potentially confounding variables that will show an at least marginally significant (p < .10) difference between groups. The analyses concerning the subgroup effects will be conducted on the sample as a whole, whereby possible moderating variables, like complications and personality will be included in the analyses as between-subjects factors. All analyses will be based on the intention-to-treat approach.

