**Methods/Design:**

The Diabetes and Mindfulness study (DiaMind) is a randomized controlled trial. Patients with diabetes with low levels of emotional well-being will be recruited from outpatient diabetes clinics. Eligible patients will be randomized to an intervention group or a wait-list control group. The intervention group will receive the mindfulness program immediately, while the control group will receive the program eight months later. The primary outcome is emotional distress (anxiety, stress, depressive symptoms), for which data will be collected at baseline, four weeks, post intervention, and after six months follow-up. In addition, self-report data will be collected on quality of life, dispositional mindfulness, self-esteem, self-care, and personality, while complications and glycemic control will be assessed from medical files and blood pressure will be measured. Group differences will be analyzed with repeated measures analysis of covariance.

The study is supported by grants from the Dutch Diabetes Research Foundation and Tilburg University and has been approved by a medical ethics committee.

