### Randomization

After the inclusion of every 16 to 20 patients the participants will be randomized into two groups: the intervention group and the control group. The randomization will be done as follows. After the interview and upon receipt of a signed informed consent form, the patient will be assigned to a participant number. Subsequently the participant will receive the baseline questionnaire by mail or email. When the first author receives the baseline assessment, she passes on the corresponding participant number to the second author who has no further involvement in the practical recruitment, enrolment, and assessment of the patients. The second author will refer to the computer generated (through PASW Statisitics 17) random list (uneditable and concealed for others) prepared by a statistician with no involvement in the trial. The second author will inform the first author about the allocation by email and will archive the allocations in a secured document on his computer. The first author will document the allocation in the general inclusion database, which will be checked by the second author. The first author will inform the patients both by telephone and letter about their allocation. The above described procedure will eliminate experimenter bias in group assignment. The computer program the statistician will use utilizes a random number generator and will be programmed to insure equal numbers of subjects in each arm of the study within a block of 4 participants.

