The recruitment has already started in the Catharina Hospital in Eindhoven in spring 2010 and in the Maxima Medical Center in autumn 2010. At present, 969 individuals have been screened for emotional problems. Of those, 811 did not qualify: 658 had a score above 12 on the WHO-5 screening instrument, and 153 were ineligible (no mastery of the Dutch language, psychiatric disorder, or severe physical condition). Of the eligible patients, 120 declined participation (no perceived need or motivation for the training or an incompatible working schedule). At present, 42 patients are interested to participate, of whom 16 have been enrolled so far.

The recruitment of a sufficient number of patients will be a challenge. For instance, the mindfulness intervention requires participants to commit to attending eight two-hour group sessions and to practice exercises at home for five days per week. For people who have busy lives this sometimes is a challenge to comply with, which may make them decline participation or drop out of the study.

Concerning the benefits of the present study, the results will provide valuable information regarding the effectiveness of the mindfulness intervention for DM patients in improving emotional well-being. We will also gain insight in the pros and cons of a possible implementation of the intervention in usual medical care of DM patients. By doing this, we aim to find ways that can contribute to increased emotional well-being and quality of life in patients with diabetes mellitus.

In conclusion, considering the prospected increase of the prevalence of diabetes, the levels of emotional distress in this patient group, and the incompleteness of the current literature on effective psychological interventions for the distressed patients, well-designed trials on psychological interventions are a welcome addition in the diabetes research. In the present randomized controlled trial the effectiveness of a psychological intervention will be examined in which the cultivation of mindfulness (the direction of attention to one's experiences in the present moment in an open and accepting manner) plays a central role. This intervention may be an effective alternative to traditional cognitive behavioral therapy in improving emotional well-being in DM patients. The first results of the study will become available in 2012.

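### Unless missing values are imputed, the named repeated measures (M)ANCOVA excludes every patient with a missed modelled assessment and so does not deliver the stated intention-to-treat analysis

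*Protocol article*

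**What the plan says.** The Planned analyses section of the protocol article fixes the method: "Repeated measures analysis of variance ((M)ANCOVA) will be used to test the hypotheses". It closes with the analysis principle: "All analyses will be based on the intention-to-treat approach". For the primary outcome the abstract says that "data will be collected at baseline, four weeks, post intervention, and after six months follow-up". In Table 1 these are T1, T2, T3 and T5; T4 is for HbA1c only.

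The article expects losses. The sample size section lists "patient attrition" among the things allowed for, and the Discussion says of the time demands of the training, "which may make them decline participation or drop out of the study". The target is worded as follows: "The total number of patients that have to be included and complete the study is 160, with 80 patients in each arm".

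The article does not say how missing questionnaires will be handled. It mentions no restriction to complete cases, no imputation and no likelihood-based model.

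**The concern.** Classical repeated measures (M)ANCOVA works on one row per patient and needs every repeated value in that row. A patient who misses only T2 leaves the whole model, and the valid T3 and T5 scores go too. If the multivariate form is run jointly on several primary scales, one missing scale has the same effect.

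Two things are at stake.

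- **Who is compared.** Until T5 only the intervention arm attends sessions and does homework; the control arm starts its training at T5. Reasons for not completing can therefore differ between the arms, and a comparison of completers loses some of the protection of randomisation. Outcomes are self-reported by unblinded patients, so non-response may also be related to perceived benefit.
- **Data thrown away.** Follow-up scores already collected from partial responders do not contribute.

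**Working it through.** **Inputs from the article**
- Repeated primary measurements: T1, T2, T3, T5.
- T1 is in hand before allocation: "When the first author receives the baseline assessment, she passes on the corresponding participant number to the second author". Missingness in the repeated outcome therefore arises mainly at the three follow-ups.
- 80 patients per arm, alpha 0.05, power 0.80.
- Effect size: "taking into account a medium effect size", with no number.
- Attrition: expected, with no rate.

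**Assumptions**
- d = 0.5, two-sided test.
- 80 per arm is the number randomised. The sample size wording could also mean 80 completers.
- A range of missingness rates and two patterns.
- Power is for an unadjusted two-group comparison at one visit. It is a yardstick, not the power of the covariate-adjusted repeated measures test.

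**Step 1: the plan's own figure.** n per arm = 2 × (1.960 + 0.842)² / 0.5² = 62.8, so 63 (64 with the t distribution). Then 64 / (1 − 0.20) = 80 per arm, or 160 in total. The stated figure is met with d = 0.5 and about 20% attrition. The article gives neither number, so its own inputs do not determine 160.

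**Step 2: listwise deletion with independent missingness m at each of T2, T3 and T5.** Complete share = (1 − m)³. Power ≈ Φ(0.5 × √(n/2) − 1.96).

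| m | Complete share | Complete per arm | Power | Available at one visit, per arm | Power |
|---|---|---|---|---|---|
| 5% | 0.857 | 68.6 | 0.83 | 76 | 0.87 |
| 10% | 0.729 | 58.3 | 0.77 | 72 | 0.85 |
| 15% | 0.614 | 49.1 | 0.70 | 68 | 0.83 |
| 20% | 0.512 | 41.0 | 0.62 | 64 | 0.81 |

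Worked row, m = 10%: 0.9³ = 0.729; 80 × 0.729 = 58.3; 0.5 × √29.16 − 1.96 = 0.74; Φ(0.74) = 0.77. With the t distribution this is 0.76.

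**Step 3: purely monotone dropout by T5.** Complete cases per arm are 80 × (1 − dropout).
- 10%: 72 per arm, power 0.85.
- 20%: 64 per arm, power 0.81.
- 30%: 56 per arm, power 0.75.

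**Step 4: the mechanism.** One data set of 160 patients was simulated with 10% missing at each of three follow-ups. The MANOVA used 114 patients (160 × 0.729 = 117 expected). A mixed model on the same data used all 160, with 429 follow-up observations.

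**The case against.** The strongest reply is that the article names a test and a principle and is silent on missing data. A condensed article may leave that to the full protocol or the SAP, neither of which is shown. Imputing before the (M)ANCOVA would keep every randomised patient. Intention-to-treat may also mean only analysis by allocated arm whatever the attendance, and a patient who stops the training can still return questionnaires by internet or post. All of this stands. A reader might infer that the planned analysis is a complete-case analysis, or that the method and the principle cannot both hold. The article does not support either inference, and its silence on imputation is not the fault raised here.

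A reader might also infer that the estimate is biased in favour of the training. That needs missingness that differs by arm and is related to outcome. The article gives no attrition by arm. Wait-list patients might leave, or might stay because training is promised to them. If missingness is completely at random, the loss is one of precision only.

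The power figures also have limits. For a given rate per visit, independent missingness removes far more patients than monotone dropout does. The fair comparison at 10% is 0.77 against about 0.85, and not against the 0.885 of a trial with no missing data, which no method would reach. If 160 means completers, the fall to 58 per arm does not follow.

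What remains is that the article did choose a method, and under the attrition it expects that method does not by itself deliver the stated principle.

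**Conclusion.** The point holds in conditional form. Without imputation, the named (M)ANCOVA leaves out each patient with a missed assessment in the model, and so does not analyse all randomised patients. For the primary outcomes the relevant assessments are T1, T2, T3 and T5. A missed T4 has no effect on them, and the secondary questionnaires are not taken at T2.

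The main issue is the analysis population and the possible bias, whose direction is unknown. Power is secondary and depends on the pattern of missingness: a modest avoidable loss if 10% miss each follow-up independently, and power still just above the planned 0.80 if 20% drop out monotonically. These sizes rest on d = 0.5, 80 randomised per arm and the assumed rates. The two statements should be reconciled before the analysis, because they decide who counts in the primary comparison.

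**What to change.** Do one of the following in the Planned analyses section.

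- **Preferred:** replace the (M)ANCOVA with a likelihood-based linear mixed model for repeated measures. Use arm, time, arm × time, the baseline score and the pre-set covariates as fixed effects, and include all available follow-up data with patients analysed as allocated, whatever their attendance.
- **Alternative:** keep the (M)ANCOVA, but apply pre-specified multiple imputation first.

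In either case add one missing-not-at-random sensitivity analysis that includes patients with no follow-up. A mixed model of follow-up scores omits those patients, so without this step it would also fall short of all randomised patients. Which time point is the primary contrast is a separate design decision that this change does not settle.

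The cost is revised wording and a little more programming in standard software. No new data or visits are needed.

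### Covariates beyond age, sex and co-morbidity are chosen by testing the randomised groups at p < .10, and the stated list does not name each outcome's T1 score

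*Protocol article*

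**What the plan says.** All of this is in the protocol article.

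- **Model.** The section on planned analyses names the method as follows: "Repeated measures analysis of variance ((M)ANCOVA) will be used to test the hypotheses concerning the differences between groups on the dependent variables over time". The abstract (Methods/Design) says: "Group differences will be analyzed with repeated measures analysis of covariance".
- **Fixed covariates.** Planned analyses: "In these tests age, sex, and co-morbidity will be included as covariates".
- **Added covariates.** The same sentence continues: "in addition to those other potentially confounding variables that will show an at least marginally significant (p < .10) difference between groups". The candidate variables are not listed.
- **Allocation.** Randomization describes a computer-generated list, hidden from those who enrol patients and "programmed to insure equal numbers of subjects in each arm of the study within a block of 4 participants". A participant is allocated only after the baseline questionnaire has come back.
- **Baseline data.** For the primary outcome, "data will be collected at baseline, four weeks, post intervention, and after six months follow-up". Table 1 shows a T1 measurement for every questionnaire outcome, for HbA1c and for blood pressure. It also lists a 21-item background form. Demographic and clinical variables describes part of what is collected: "Data will be collected regarding the participant's age, marital status, education, and job status", followed by a range of clinical and psychological items.

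**The concern.** The baseline questionnaire precedes a concealed random allocation, so a baseline difference between arms can only be chance. Testing for one does not show whether a variable matters. What matters for precision is whether the variable predicts the outcome, and the rule does not look at that. It can bring in a weak predictor that happens to be imbalanced and leave out a strong one that happens to be balanced.

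The final covariate set also cannot be written down before the data are seen, because it depends on which imbalances occur in a pool that the article does not define.

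The T1 score of each outcome is likely to be among its best predictors and is already collected, but it is not among the named covariates. On the stated rule it would become a covariate only if it counted as a potential confounder and happened to differ between arms. What is at stake is mainly precision, in a trial whose Discussion calls recruitment a challenge and reports 16 enrolled after 969 screened.

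**Working it through.** **Inputs.** From the article: threshold 0.10; "The total number of patients that have to be included and complete the study is 160, with 80 patients in each arm"; a medium effect, power 0.80 and alpha 0.05. Assumed: medium means d = 0.5; alpha is two-sided; candidates are independent; the correlation rho between T1 and follow-up is 0.3 to 0.7; the outcome SD is equal at both times. The article gives neither rho nor the pool size.

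**1. The plan's own figure.** At d = 0.5, 63 per arm are needed (64 with the t distribution). The stated 80 follows if 20% attrition is assumed: 64/(1 − 0.20) = 80. The article gives no attrition rate and describes 160 as patients who must complete, so the figure cannot be reproduced from its own inputs. The present point does not depend on it; 80 per arm is used below only as the planned size.

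**2. How often the rule adds something.** Each chance test passes with probability 0.10. With k candidates the expected number added is 0.10k, and P(at least one) = 1 − 0.9^k.

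| k | expected | P(at least one) |
|---|---|---|
| 5 | 0.5 | 1 − 0.590 = 41% |
| 10 | 1.0 | 1 − 0.349 = 65% |
| 20 | 2.0 | 1 − 0.122 = 88% |

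**3. What the rule does to the test.** A simulation used 4,000 trials with 80 per arm and 10 candidates. One candidate was prognostic, explaining 25% of the variance left after T1. Type I error was as follows.

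| Analysis | rho 0.5 | rho 0.7 |
|---|---|---|
| Change score, no selection | 4.7% | 5.1% |
| Change score, p < .10 selection | 3.9% | 3.9% |
| T1 as fixed covariate | 4.8% | 5.1% |

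The Monte Carlo standard error at 5% is √(0.05 × 0.95/4000) = 0.34 percentage points. The 3.9% is therefore a real but small shortfall, in the conservative direction.

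**4. T1 as response or as covariate.** For one follow-up and outcome SD 1, the change-score variance is 2(1 − rho) and the variance adjusted for T1 is 1 − rho². The ratio is (1 − rho)(1 + rho)/[2(1 − rho)] = (1 + rho)/2. Power at d = 0.5 with 80 per arm is Φ(0.5/√(2v/80) − 1.96), where v is the relevant variance.

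| rho | v, change | v, T1 covariate | ratio | power, change | power, T1 covariate | n per arm for 80% power |
|---|---|---|---|---|---|---|
| 0.3 | 1.40 | 0.91 | 0.65 | 76.2% | 91.2% | 88 v 58 |
| 0.5 | 1.00 | 0.75 | 0.75 | 88.5% | 95.5% | 63 v 48 |
| 0.7 | 0.60 | 0.51 | 0.85 | 98.3% | 99.3% | 38 v 33 |

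The simulation agrees. At d = 0.5, the change score with selection had power 87.9% (rho 0.5) and 98.5% (rho 0.7), against 95.1% and 99.4% with T1 as a fixed covariate. The SD of the estimate was 0.158 v 0.139 and 0.118 v 0.114.

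**5. Where the loss comes from.** Selection did not make the change score worse: without it, power was 87.2% and 98.2%. Most of the gap in step 4 is thus change score against T1 adjustment. The loss due to the rule itself is relative to a fixed list: a balanced prognostic variable is left out about 90% of the time.

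**The case against.** The strongest case on the other side has four parts.

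- **Much of the model is fixed.** Age, sex and co-morbidity enter whatever the balance. The rule and its threshold are stated in advance and refer to group differences, not to outcome results. Masking says that the statistician will be blinded to allocation. This stands: only the added covariates depend on the data, and nothing suggests that they would be chosen to favour an arm. It does not make chance imbalance a sensible criterion.
- **The p-values are not shown to be too small.** A reader might infer that data-dependent adjustment inflates type I error. The simulation shows the opposite, so that reading is not supported.
- **The pool may be small.** A reader might take all 21 background items and more as candidates and conclude that an addition is almost certain. The article limits the pool to potential confounders, and the form includes age and co-morbidity, which are already fixed. Only a range can be given. Nor does the article say that variables measured after randomisation would be tested, so adjustment for mediators cannot be read into it.
- **The handling of T1 is not stated.** A reader might infer that baseline is ignored, or that T1 certainly enters only as a response. The article says neither. Analysing differences over time makes T1 as first response the likely reading, but a condensed article may leave this to the full plan. This stands, so the T1 part is conditional. The ratio (1 + rho)/2 is for a single follow-up, whereas the primary questionnaires have three follow-ups (T2, T3, T5) before the control group starts training.

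**Conclusion.** The point holds as a should-fix. The p < .10 rule is written in the plan and is unsuitable for a randomised comparison: it selects on chance imbalance and leaves part of the model open until the data are seen. How often it would act depends on an unlisted pool, about 41% to 88% for 5 to 20 independent candidates. The harm is lost precision against a fixed prognostic list and slight conservatism; neither bias nor type I inflation is shown.

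The omission of T1 from the named covariates is a fact of the text, but its cost is conditional. If T1 serves only as the first repeated response, adjusting for it would reduce the variance to 0.65 to 0.85 of the change-score value, for a single follow-up and an assumed rho of 0.3 to 0.7. At 80 per arm and d = 0.5 this is a clear gain at low to moderate rho and a small one at 0.7. Change scores fall below 80% power only at the low end of that range (76.2% at rho 0.3).

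**What to change.** In Planned analyses:

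1. Delete the p < .10 rule.
2. State for every outcome the same fixed covariates: the T1 score of that outcome, age, sex and co-morbidity.
3. State that the repeated responses are the post-baseline measurements up to T5: T2, T3 and T5 for the primary questionnaires, and for other outcomes the follow-ups that Table 1 gives.
4. Describe baseline balance without significance tests.
5. Label any other adjustment as a sensitivity analysis.

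This is a wording change, to be made before the data are analysed. Every T1 score is already collected, and neither the sample size nor the assessment schedule changes. The cost is one degree of freedom per outcome for the T1 score.
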